## Abstract

**Background:** Traditional Chinese medicine (TCM), a main form of complementary and alternative medicine provides a potential possibility for demyelinating disease of the central nervous system (DDC) management and has been applied in considerable amounts of patients with this disorder. Nevertheless, powerful real-world evidences regarding the epidemiological and clinical characteristics, safety, and outcomes of TCM in DDC are lacking. The primary objective of the Demyelinating Diseases of the Central Nervous System Registry for Patients with Traditional Chinese Medicine (DATE-TCM) is to create an organized multicenter data collection structure to define integrative characteristics of DDC patients treated with TCM in an endeavor to fill these knowledge gaps to better inform clinical care and health policy.

**Method:** This study provides a prospective and voluntary registry by using a web-based system. Baseline data will be recorded and subsequently regular follow-up visits will be implemented every 3–6 months for a total of 5 years. The primary outcome is Annualized Aggregate Relapse Rate at 5-year follow-up.

**Results:** DATE-TCM is currently designed to capture the multidimensional (epidemiologic, demographic, clinical, etc.) features of DDC patients receiving TCM treatment, the type and long-term safety and efficacy of TCM intervenes in the DDC populations, as well as the interaction of TCM treatments and disease modifying therapies in the management of DDC, aiming to include 2000 eligible adult DDC patients with TCM intervenes from 35 participating centers, covering 77.4% of provincial administrative regions of mainland China.

**Conclusion:** DATE-TCM is the first, largest, most geographically extensive, and standard registry-based observational study that systematically document the real-world data regarding the TCM application in the DDC populations, which will be extraordinarily important for clarifying the comprehensive characteristics and outcomes of TCM in DDC, further shed light on standardizing and optimizing the TCM measures for DDC management and establishing evidence-based clinical practice guidelines for TCM application in DDC.

**Clinical Trial Registration:**
clinicaltrials.gov, identifier NCT05415579.

## 1 Introduction

Demyelinating Diseases of the Central Nervous System (DDC) is a collective term for a group of autoimmune-mediated inflammatory disorders in young adult age, mainly including multiple sclerosis (MS), Neuromyelitis optica spectrum disorder (NMOSD), and myelin oligodendrocyte glycoprotein (MOG)-associated disease (MOGAD), characterized by myelin loss and axonal damage of the central nervous system (CNS) (Chen et al., 2021). Depending on the functional neuronal system affected, there is a diversified spectrum of possible symptoms of DDC, such as paresthesia, limb weakness, visual impairment, balance disturbance, and bladder or bowel dysfunction, resulting in neurological disability of the patients (Hoftberger and Lassmann, 2017). MS is thought to occur most frequently in Western Europe and North America, while the highest incidence of NMOSD has been reported in Afro-Caribbean region (Bishop and Rumrill, 2015; Papp et al., 2021). In China, epidemiological data suggests that the incidence of NMOSD (0.278/100,000 person years) is slightly higher than that of MS (0.235/100,000 person years) (Tian et al., 2020a; Tian et al., 2020b). Since MOGAD is a newly defined disease entity in 2018, its epidemiological information within specific regions or worldwide has not yet been clarified (Lopez-Chiriboga et al., 2018). Currently, a range of injectable disease-modifying therapies (DMTs) such as glatiramer acetate, several interferon-beta regimens, natalizumab, rituximab, satralizumab, and oral DMTs such as fingolimod, dimethyl fumarate, teriflunomide have become available for DDC treatment (McGinley et al., 2021; Wallach et al., 2021). However, not all patients respond well to their prescribed DMTs, manifesting limited efficacy and side effects (progressive multifocal leukoencephalopathy, infections, gastrointestinal side-effects, leukopenia, arthralgia) that may require additional management.

Patients suffering from DDC are more likely to seek help from complementary and alternative medicine (CAM), which is used by 57%–81% of patients with MS in developed country (Nayak et al., 2003; Apel et al., 2006; Schwarz et al., 2008; Ng and Kishimoto, 2021). Traditional Chinese medicine (TCM), a major form of CAM, including Chinese herbal medicine (CHM), acupuncture and other non-medication therapies provides a potentially valuable possibility for DDC treatment. A prospective clinical study investigating factors associated with CAM usage in MS patients in the United States indicated that the three most common CAMs used by patients with MS were chiropractor, massage, and acupuncture, and the most frequent reasons for CAM use were symptom relief, back problems, and pain (Kim et al., 2018). A systematic review and meta-analysis including 20 randomized-controlled trials (RCTs) and 1,100 participants assessing the efficacy and safety of CHM as an adjunct therapy of patients with MS demonstrated significant effects of CHM on improving Expanded Disability Status Score (EDSS), annual relapse frequency, and overall clinical efficacy rate compared with conventional western treatments (Song et al., 2017). Also, in this review, six studies monitoring the adverse effects of CHMs in MS treating showed that CHMs were well tolerated in all patients. In addition, acupuncture has been reported to be effective in reducing spasticity, pain, and numbness and improving fatigue, imbalance, and motor function in patients with DDC (Criado et al., 2017; Khodaie et al., 2022). Nevertheless, it is worth noting that poor methodological quality, comparatively prominent clinical heterogeneity, and small sample size are common problems in most RCTs on TCM. Therefore, favorable evidence-based studies remain scarce and many physicians remain skeptical about the use of TCM in DDC management, which directly affects the feasibility of TCM treatment and limits the widespread application of TCM in the DDC populations.

Although RCTs provide useful information on the effectiveness of DDC therapies, lines of evidence suggests that long-term and prospective databases or registries of large inception cohorts could include various domains such as demographic, disease course, medication status, socio-economic data, and auxiliary examination results, which is expected to provide the best understanding of the natural history, epidemiology, and clinical characteristics of DDC and the long-term effectiveness of treatments that cannot be captured in any other way. Accordingly, regional or national MS or DDC registries have been established for decades, including the German MS registry, the Italian MS registry, the Danish MS registry, the Swedish MS registry, the Norwegian MS Registry and Biobank, the European Database for MS, the North American Research Committee on MS (NARCOMS), and the MSbase, which support comparative effectiveness studies, provide important insights into the epidemiology and outcomes of DDC, and offer valuable patient perspectives. (Flachenecker and Stuke, 2008; Flachenecker et al., 2014; Traboulsee, 2014). In China, there are several single- or multi-centers prospective registries for DDC (NCT03514030, NCT04101058, NCT04106830, NCT05154370, ChiCTR2000030651), all of which are based in Western medicine hospitals and mainly focus on elucidating the epidemiologic, clinical, imaging features of DDC, as well as the treatment response to DMTs. To the best of our knowledge, there is still a lack of powerful real-world evidence regarding the epidemiological and clinical characteristics, safety, and outcomes of TCM in DDC. Therefore, the primary objective of the Demyelinating Diseases of the Central Nervous System Registry for Patients with Traditional Chinese Medicine (DATE-TCM) is to define the multidimensional (epidemiologic, demographic and clinical, etc.) characteristics of DDC patients receiving TCM treatment, the type and long-term safety and efficacy of TCM intervenes in DDC populations, and the interaction of TCM treatments and DMTs in the management of DDC, with the aim of filling the above knowledge gaps and provide a better inform for clinical care and health policy.

## 2 Method and analysis

### 2.1 Study design

DATE-TCM is a prospective, multi-center, observational, disease-based registry of DDC patients treated with TCM in a real-world setting, designed to determine the general characteristics of DDC patients treated with TCM, the types of TCM intervenes, the long-term safety and efficacy of TCM treatment, and the interaction of TCM intervenes and DMTs in the management of DDC. The registry protocol follows the Declaration of Helsinki and Tokyo guidelines for humans and was approved by the Ethics committee of Dongzhimen Hospital, Beijing University of Chinese Medicine (2022DZMEC-171-02) as the coordinating center and will be approved by the local ethics committee of all participant centers. Prior to inclusion in the DATE-TCM, patients or their legally authorized representatives are informed of their conduct by medical staff and must sign a written informed consensus before data collection commences. In this consent form, patients can give permission for relevant biological specimens to be collected and their data to be used for further research activities. Patient participation will be entirely voluntary, with the ability to withdrawal from DATE-TCM participation at any time, and without the need to provide an explanation.

### 2.2 Participants

#### 2.2.1 Key inclusion criteria

(1) Male or female participants aged ≥18 years old;(2) Diagnosis of DDC according to relevant criteria or consensus, including MS, NMOSD, and MOGAD (Wingerchuk et al., 2015; Lopez-Chiriboga et al., 2018; Thompson et al., 2018);(3) Patients are treated with TCM intervenes, including the CHM, acupuncture, moxibustion, massage, taiji, and qigong;(4) Obtain informed written consent from the patient, and/or his/her legally authorized representatives.

#### 2.2.2 Key exclusion criteria

(1) Refusal to give informed consent;(2) Malignancies, infectious diseases (HBV, HCV, HIV, etc.), congenital or acquired severe immunodeficiency, significant cardiovascular, pulmonary, and hepatic diseases or conditions;(3) Mental disturbance or severe cognitive impairment impeding necessary information collection and assessment.

### 2.3 Site selection and study sample size

Participant centers were recruited nationwide from each region of mainland China on a voluntary basis. They must meet the following criteria: 1) the ability to accurately diagnose DDC; 2) the ability to admit over 30 patients with DDC per year; 3) be able to complete relevant data upload and biospecimens collection in accordance with the database requirements. Currently, DATE-TCM possesses a total of 35 qualified participant centers, covering 77.4% of provincial administrative regions in mainland China (Figure 1). And the number of participating centers is gradually expanding, with the goal of exceeding 50. Based on estimate of at least 30 cases treated per participating center annually, the total number of patients for the 35 centers is 1,050 per year. By the end of the second year after enrollment commences, up to 2000 patients are expected to be enrolled. DATE-TCM is expected to begin patient recruitment on 20 June 2022.

**FIGURE 1 F1:**
[figure not shown]
Sites distribution of DATE-TCM.

### 2.4 Data collection and follow-up plan

The main variables were determined with reference to the MS or DDC Registry in Germany, Italy, Denmark, Sweden, Norway, Switzerland, as well as the European Database for MS, NARCOMS, and MSbase (Butzkueven et al., 2006; Hillert and Stawiarz, 2015; Myhr et al., 2015; Trojano et al., 2019; Magyari et al., 2021; Marrie et al., 2021; Ohle et al., 2021), and combined with the characteristics of TCM treatment (Table 1). To be noted, the compulsory common minimum dataset (MDS) was setup by expert consensus and reference to other regional or national MS or DDC registry studies, consisting of information selected to ensure that 1) sufficient data were collected to define multidimensional characteristics of the DDC populations receiving TCM treatment; 2) data collection was simple enough; 3) each participant center could achieve maximum completeness and quality; 4) facilitate the exchange and collaboration with national and international datasets. DATE-TCM database only accepts records with the completed MDS (Supplementary Table S1). In addition to the collection of data information, DATE-TCM involves the collection and storage of blood specimens for subsequent testing according to an established schedule.

**TABLE 1 T1:** Main variables and follow-up plan in the DATE-TCM.

Index	Variables	Baseline visit	Follow-up visit Every 3 months ◎
			Every 6 months ☉
			Every 12 months •
Demographic variables	Gender, year of birth, ethnicity, birthplace, present residence	○	
Socioeconomic variables	Education, working situation, occupational or educational changes due to DDC, societal context (e.g. medical insurance), marriage, reproduction, walking assistance, Full-time Nursing, TCM-related expense, Total disease-related expense	○	◎
Diagnosis variables	First symptoms and lesion locations, year of onset, diagnosis, year of diagnosis, diagnostic criteria, symptoms (lesion locations) ever, attack list (date, lesion locations or symptoms)	○	
Symptoms variables	Symptoms current, clinical type of MS, time to SPMS	○	◎
Comorbidities variables	Comorbidities, medication for comorbidities	○	◎
Risk factors and medical history	Smoking consumption, Alcohol consumption, Family history, Allergy history, Trauma history, Vaccination, Sun exposure	○	
Treatment	Any previous medication (start and end date), reasons for discontinuation	○	
	DMT current (Generic name, date of start, dose, frequency), TCM type current (TCM preparation, acupuncture, moxibustion, massage, taiji, qigong), detailed use of TCM preparations (name of TCM preparation or information on commercial products, date of start, dose, frequency, composition of TCM preparation including herbal, animal, mineral, and other natural materials, forms of TCM preparation including pills, powders, soft extracts, pellets, decoctions, and medicated liquor), Additional medicine/supplements	○	◎
Safety assessments	AEs, SAEs		◎
CSF	LP date, LP performed at (relapse/remission), Number of Mono and leukocytes, protein content, OCB, IgG index, anti-AQP4 IgG, anti-MOG IgG	○	◎
MRI	MRI date, T2 lesions (total number), New or enlarged T2 lesions (number), Gd-enhanced T1 lesions (total number), Quantitative/volumetric MRI, Brain Parenchymal fraction, Normalized total brain volume, Normalized total lesion volume in white matter	○	•
Other examinations	Evoked potentials (Visual, Somatosensory, Brainstem)	○	◎
	Blood leukocyte count and classification count, Blood liver and renal functions test, Serum NFL, Serum cytokines, Serum anti-AQP4 IgG, Serum anti-MOG IgG	○	☉
Specific scales	BMI, EDSS	○	◎
	MSFC, SDMT, FSS, MSIS, EQ-5D	○	☉
Four examinations of TCM	Inspection, listening and smelling examination, inquiry, palpation	○	◎
Relapse	Relapse date, Affected functional system, severity, Any treatment performed, recovery after relapse		◎

Note: DDC, demyelinating Diseases of the Central Nervous System; MS, multiple sclerosis; SPMS, secondary progressive multiple sclerosis; DMT, disease modifying therapy; TCM, traditional Chinese medicine; CSF, Cerebro-Spinal Fluid; AEs, adverse events; SAEs, severe adverse events; LP, lumbar puncture; OCB, oligoclonal bands; AQP4, Aquaporin-4; MOG, myelin oligodendrocyte glycoprotein; MRI, magnetic resonance imaging; NFL, neurofilament light chain; BMI, body mass index; EDSS, expanded disability status scale; MSFC, multiple sclerosis functional composite; SDMT, symbol digit modalities test; FSS, fatigue severity scale; MSIS, multiple sclerosis impact scale; EQ-5D, EuroQol-5D.

The follow-up plan was developed with reference to the relevant elements of DDC registry studies from other regions or countries and the characteristics of TCM treatment. Demographics, symptoms, and comorbidities variables, treatment status, safety assessments, Cerebro-Spinal Fluid (CSF) or other examinations (e.g., evoked potentials) results, Body mass index (BMI), EDSS, four examinations of TCM, and relapse information will be follow-up every 3 months by telephone or face-to-face visits. The Multiple Sclerosis Functional Composite (MSFC), Symbol Digit Modalities Test (SDMT), fatigue severity scale (FSS), Multiple Sclerosis impact scale (MSIS), and EuroQol-5D (EQ-5D) assessments will be administrated every 6 months through face-to-face visits. Blood leukocyte count and classification count, blood liver and renal functions test, serum neurofilament light chain (NFL), serum cytokines, serum anti-AQP4 IgG, and serum anti-MOG IgG will be tested every 6 months. MRI related evaluation of brain and spinal cord will be conducted every 12 months.

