### 2.6 Outcome measurements

The primary and secondary outcomes are listed in Table 2. The primary outcome is the Annualized Aggregate Relapse Rate, defined as the number of confirmed relapses within a year. A relapse is defined as the appearance of a new or worsening previously stable or improving pre-existing neurological abnormality, separated by at least 30 days from onset of a preceding relapse. Such abnormalities must be present for at least 24 h and occur in the absence of fever or infection.

**TABLE 2 T2:** The outcomes of DATE-TCM study.

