**Secondary outcomes**
Total number of adverse events during evaluation
Percentage of participants with adverse events
Time to 3-month sustained disability progression
Time to 6-month sustained disability progression
Number of new or newly enlarging T2 hyperintense lesions as measured by magnetic resonance imaging (MRI)
Number of gadolinium-enhancing T1-weighted lesions as measured by MRI
Percent change in brain volume as measured by MRI
Change in multiple sclerosis functional composite (MSFC) score
Change in symbol digit modalities Test (SDMT) score
Chance in fatigue severity scale (FSS) score
Change in euroQol- 5 dimension (EQ-5D) score
Change in multiple sclerosis impact scale (MSIS) score

The Secondary outcomes include total number of adverse events (AE, any unfavorable and unintended sign, symptom, syndrome, or illness observed by the investigator or reported by the participant during the study), percentage of participants with AE, time to 3-month sustained disability progression (disability progression was defined as an increase from baseline in EDSS score of at least 1-point or at least 0.5-point for participants with baseline EDSS score >5.5), time to 6-month sustained disability progression, number of new or newly enlarging T2 hyperintense lesions, number of gadolinium-enhancing T1-weighted lesions, percent change in brain volume, change in MSFC score, change in SDMT score, chance in FSS score, change in EQ-5D score, and change in MSIS score.

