### 2.9 Data analysis

As for the continuous variable, normality test was performed for all index awaiting assessment. If it is in accordance with normal distribution, it will be described as mean with 95% confidence interval (CI) or with standard deviation (SD), and one-way analysis of variance (ANOVA) was used for comparison in 3 or more groups, independent sample *t*-test was used for comparison in 2 groups, and Pearson correlation was used for correlation analysis between index. If not, it will be described as median with range or interquartile range (IQR), and Kruskal–Wallis one-way ANOVA was used for comparison among 3 or more groups, Mann-Whitney *U* test was used for comparison between 2 groups, and Spearman correlation was used for correlation analysis between index. Regarding categorical variable, it will be presented as frequencies or proportions, and tested by Fisher exact test. Kaplan-Meier method consists of calculating the probabilities of non-occurrence of event at any observed time of event. The Cox proportional-hazards regression model will be used to investigate the association between the survival time or time of event of patients and one or more predictor variables. Subjects with incomplete data will also be included in the analysis. For each variable, the number of subjects with missing data will be documented. Defining the multidimensional characteristics of DDC patients receiving TCM treatment, the types and detailed information of TCM in DDC treatment, as well as possible combinations of TCM treatments and Western medications are significant objectives of DATE-TCM. Based on these objectives, we did not impose any restriction on patients receiving TCM intervenes or western medications or both at different centers, and the relevant information was recorded systematically for further relevant descriptive studies. Notably, determining the long-term safety and efficacy of TCM interventions in the DDC population and the interaction of TCM treatments with DMTs are important goals for the establishment of DATE-TCM as well. The related studies could be performed based on the established registry data with subsequently systematic cases screening and identification criteria for different study purposes (e.g., the efficacy of a specific TCM preparation or a specific combination of TCM preparation and DMT) in order to obtain a relatively consistent treatment context of patients in a given study. Moreover, propensity score methods will be applied in these comparative studies to control for confounding factors to ensure baseline comparability between groups before evaluating the impact of a treatment on expected clinical end point events. Additionally, we will continue to appropriately adapt the detailed statistical methods according to the characteristics and needs of each DATE-TCM-based study. Values of *p* < 0.05 were considered to indicated statistical significance. All data sets were analyzed using SPSS 21.0 Software or Program R (Version 3.5.1).

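### As written, the 3-monthly EDSS may be taken by telephone or in person, and two sustained-progression outcomes use the scores without distinguishing mode; record the mode and add a face-to-face sensitivity analysis

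*Protocol article*

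**What the plan says.** Section 2.4 sets contact mode in two consecutive sentences. The first covers the 3-monthly items: "EDSS, four examinations of TCM, and relapse information will be follow-up every 3 months by telephone or face-to-face visits". The second covers MSFC, SDMT, FSS, MSIS and EQ-5D, whose "assessments will be administrated every 6 months through face-to-face visits". EDSS is in the first group only. Table 1 has the same split by interval (BMI and EDSS 3-monthly, the other scales 6-monthly) and lists no contact-mode variable.

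Section 2.6 defines disability progression as "an increase from baseline in EDSS score of at least 1-point or at least 0.5-point for participants with baseline EDSS score >5.5". Two secondary outcomes in Table 2 rest on it: "Time to 3-month sustained disability progression" and "Time to 6-month sustained disability progression". Neither the definition nor the table mentions how the score was obtained.

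The Abstract gives the follow-up: "regular follow-up visits will be implemented every 3–6 months for a total of 5 years". Section 2.9 plans comparative studies with propensity scores and adds that "we will continue to appropriately adapt the detailed statistical methods according to the characteristics and needs of each DATE-TCM-based study".

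**The concern.** Sustained progression is a threshold outcome on a coarse scale. It compares a baseline score, an onset score and one or more confirming scores, and the required change is 1 point, or half a point above a baseline of 5.5. If some of these scores come from an examination and others from a telephone call, a systematic difference between the modes enters the outcome directly. Extra noise in one mode does so as well.

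At stake are the two progression outcomes, both as descriptive rates and in the comparative studies planned in section 2.9. A propensity score balances baseline characteristics. It does not correct follow-up scores that were measured differently. If telephone use differs between groups, for instance by center or by type of TCM treatment, the contrast is biased. If it is similar, the rates are still distorted and the contrast may be diluted.

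A later study can restrict itself to examined scores only if the mode was stored with each score. Mode that was never captured may not be recoverable.

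**Working it through.** The article states no figure for the progression outcomes, so there is none to reproduce. The check has three parts.

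**1. Schedule (from section 2.4 and the Abstract).** Limiting case: only the required 6-monthly visits are in person.
- Follow-up scores over 5 years: 5 × 4 = 20.
- Telephone-eligible contacts: months 3, 9, …, 57 = 10. Face-to-face: months 6, 12, …, 60 = 10.
- Ceiling over the planned 2,000 patients, with full retention and every eligible contact by telephone: 10 × 2,000 = 20,000 scores.
- Pairs 3 months apart: 20 − 1 = 19. Each joins an odd and an even quarter, so all 19 cross modes.
- Pairs 6 months apart: 20 − 2 = 18, of which 9 are face-to-face at both ends and 9 telephone-eligible at both ends. If 6-month confirmation also needs the score in between, all 18 windows contain both kinds of contact.

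These are counts of exposure and do not measure bias. They fall if telephone is used less.

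**2. Threshold arithmetic.** An assumed half-point mode difference is 0.5/0.5 = the whole threshold for a baseline above 5.5, and 0.5/1.0 = half of it otherwise.

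**3. Illustration (every value assumed, none from the documents).** Truly stable patient at EDSS 3.0; baseline examined; 20 quarterly scores; examined SD 0.35; scores rounded to 0.5. An event is a rise of at least 1.0 at two consecutive scores (3-month rule) or three (6-month rule). Telephone is used either at alternate contacts, as in part 1, or at a random half of contacts. Five-year false progression, 3-month / 6-month rule:

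| Telephone versus examined | Alternating | Random half |
|---|---|---|
| No difference | 15% / 5.5% | 15% / 5.4% |
| +0.25 | 21% / 12% | 23% / 12% |
| +0.5 | 25% / 18% | 36% / 21% |
| −0.25 | 7.5% / 2.6% | 9% / 3% |
| −0.5 | 2.9% / 1.4% | 7% / 2% |
| No shift, telephone SD 0.5 | 18% / 7% | 19% / 7% |

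With all scores examined the rates are 15% / 5.5%, the same as mixing modes with no difference between them. A shift in either direction moves both outcomes, and so does extra noise alone.

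Under the same assumptions, 6-month progression taken only from examined 6-monthly scores (two consecutive) has a false rate of about 10% whatever the telephone shift. That is above the 5.5% for quarterly scores with no mode difference, because the middle score is dropped, but it no longer depends on mode.

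**The case against.** The strongest reply is that the sentence is a loose list in a condensed article. It also holds evoked potentials, CSF results and the four TCM examinations, and Table 1 includes palpation among those. Palpation cannot be done by telephone, so the phrase cannot be a mode rule for every item. The wording may follow contact frequency, and whichever mode suits each item is a natural reading. This stands as a limit on the point. It does not remove it: 35 centers, with a goal of more than 50, would each have to infer that reading, and the next sentence does restrict five scales to face-to-face contact.

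Second, a telephone procedure or a mode field may exist in the full protocol, the supplementary minimum dataset or the data-capture system. That is possible, and their absence from the article is not the finding. The finding is what the article permits: a mix of modes within one outcome.

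Third, the harm depends on a mode difference that no document gives. This is correct, and the claim is conditional for that reason.

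Fourth, the exposure is already limited: face-to-face visits every 6 months are planned, and each study may adapt its methods. That helps only if EDSS is examined at those visits and the mode is stored.

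A reader might go further and infer that the main progression definitions should be replaced by examined scores with extra in-person confirmation. The documents do not support that as a necessary change. In a separate illustration with all scores examined (assumed SD 0.3), allowing onset only at 6-monthly visits with an examined confirmation a quarter later lowers detection of a true 1-point step by the 3-month rule from 89% to 84%. Using two consecutive 6-monthly scores for the 6-month rule raises detection from 78% to 81%, but also raises false progression from 3.5% to 5.6%. Onset would be dated to within 6 months instead of 3. In a voluntary registry, worsened patients who cannot attend would go unconfirmed.

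**Conclusion.** The point holds in conditional form. Followed as written, section 2.4 allows telephone and examined EDSS scores to be mixed within the two sustained-progression outcomes of section 2.6. If the modes differ in level or noise, both outcomes are distorted, and comparisons are biased where telephone use differs between groups. The size and direction of any actual bias cannot be known from the documents. The percentages above show only that plausible-looking shifts matter, under an assumed SD of 0.35 and a stable patient at EDSS 3.0. The exposure counts assume that only the 6-monthly visits are in person.

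A reader might infer that the progression results will be invalid, or that telephone scoring is known to be wrong. The documents show neither. Nor is the primary outcome affected: the relapse rate is "defined as the number of confirmed relapses within a year" and does not use EDSS. This is a cheap improvement to two secondary outcomes, and it is best made early because contact mode may not be recoverable afterwards.

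**What to change.** 1. In section 2.4, state that EDSS is scored by examination at the existing 6-monthly face-to-face visits.
2. Record the contact mode with every EDSS score.
3. In section 2.6, keep the main definitions and add a sensitivity analysis of sustained progression on face-to-face scores only: 6-month progression from the 6-monthly visits, and 3-month progression where onset and confirmation were both examined.

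Telephone contact can stay for the quarterly follow-up of relapse, treatment and adverse events.

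The cost is one sentence in each of the two sections, one data-capture field if none exists, and a little more analysis. No visit is added. In the sensitivity analysis, onset is dated more coarsely and fewer 3-month events can be evaluated. In the limiting case of part 1 of the working, none of the 19 pairs is examined at both ends, so the 3-month version is informative only to the extent that centers also see patients in person at the intervening quarters. How many such pairs exist will itself be visible once mode is recorded.
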